## Abstract

**Background:**

In consideration of patients seeking to use traditional Chinese medicine, an evidence-based potentiality for safe and effective use of herbal medicine and acupuncture in treatment of acne vulgaris has been suggested. However, despite common use of a combination of herbal medicine and acupuncture in clinical practice, the current level of evidence is insufficient to draw a conclusion for an interaction and efficacy of herbal medicine and acupuncture. Therefore, considering these methodological flaws, this study was designed to assess the interaction and efficacy of an available herbal medicine, Keigai-rengyo-to extract (KRTE), and acupuncture for treatment of acne using the 2 × 2 factorial design and the feasibility of a large clinical trial.

**Methods/Design:**

A randomized, assessor single blinded, 2 × 2 factorial pilot trial will be conducted. Forty four participants with acne vulgaris will be randomized into one of four groups: waiting list group (WL), KRTE only group (KO), acupuncture only group (AO), and KRTE and acupuncture combined treatment group (KA). After randomization, a total of 8 sessions of acupuncture treatment will be performed twice a week in the AO- and KA groups, respectively. Patients in the KO- and KA groups will be prescribed KRTE 3 times a day at a dose of 7.4 g after meals for 4 weeks. The following outcome measurements will be used in examination of subjects: the mean percentage change and the count change of inflammatory and non-inflammatory acne lesions, the Skindex 29, visual analogue scale (VAS) and investigator global assessment (IGA) from baseline to the end of the trial.

**Trial Registration:**

The trial is registered with the Clinical Research Information Service (CRiS), Republic of Korea: KCT0000071.

## Background

Acne vulgaris is a common skin disease encountered in dermatology practice; it is caused by changes in pilosebaceous units [1,2]. It is common in adolescence and may proceed into adulthood, affecting roughly 33% of people between the ages of 15 and 44 years [3], or affecting nearly 80% of adolescents and young adults aged 11 to 30 years [4].

Acne vulgaris is a chronic dermatosis of the pilosebaceous follicle with four fundamental etiopathogenic factors: sebaceous hyperproduction, follicular hyperkeratinization, increase of *Propionibacterium acnes *colonization, and periglandular dermal inflammation [5]. Western medical treatment options generally target one or more of the factors implicated in these acne pathogeneses [6] with topical or systemic agents, phototherapy narrowband light (blue or red), and acne vaccines [7-9].

Despite this treatment for care of acne vulgaris, a substantial number of acne patients widely seek to use traditional Chinese medicine (TCM) due to a lack of response to western medical treatment [10] and their concern regarding side effects, such as burning, erythema, desquamation, pigmentation, xerosis, and chapped lips, among others [11-15].

Herbal medicine and acupuncture are two of the major tools of TCM therapy and have been frequently administered for treatment of acne symptoms in clinical practice worldwide, particularly in East Asia [16]. In South Korea, Japan, and China, the evidence-based potentiality for safe and effective use of herbal medicine and acupuncture in treatment of acne vulgaris has been suggested [17-27]. However, the current level of evidence is poor due to the small number of good quality studies, small sample size, short duration, and variation in the composition of herbal interventions or acupuncture [28]. In addition, despite common use of a combination of herbal medicine and acupuncture in clinical practice, these studies have rarely demonstrated an interaction between herbal medicine and acupuncture, and have rarely used a waiting list- or western medical treatment group as a control group.

Considering these methodological flaws, we will conduct a trial to assess the interaction effect and efficacy of Keigai-rengyo-to extract (KRTE) and acupuncture using the 2 × 2 factorial design and the feasibility of a large clinical trial. KRTE is an herbal medicine that is often prescribed for treatment of acne; it is approved by the Korea Food and Drug Administration. Females, through the menstrual cycle, can be easily affected by the level of sex hormones, such as estrogen and androgen, relevant to increased sebum production, which play a central role in development of acne; therefore, we will restrict the participants to male patients with acne vulgaris [2,29].

## Method/Design

### Objective

The aim of this study is to investigate the efficacy and interaction of KRTE in male patients with acne vulgaris and evaluate the feasibility of a large clinical trial.

The null hypothesis is as follows: (1) there is no interaction of KRTE and acupuncture treatment on mean percent change of inflammatory acne lesions between baseline and the end of the trial; (2) mean percent change of inflammatory acne lesions between baseline and the end of the trial is equal in both the KRTE treatment group and the waiting list group; (3) mean percent change of inflammatory acne lesions between baseline and the end of the trial is equal in both the acupuncture treatment group and the waiting list group.

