### Design

This study is a randomized, 2 × 2 factorial, waiting list controlled, assessor single blinded and single-center pilot trial.

The study will be sequentially conducted as follows: enrollment after screening via inclusion and exclusion criteria, randomization, a treatment period of 4 weeks, and assessment (Figure 1).

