### Intervention

#### KRTE

KRTE is approved by the Korea Food and Drug Administration as a prescription in clinical practice for patients with sinusitis, otitis media, and acne. The components of KRTE are presented in Table 1. The authors purchased KRTE from the Han Kook Sin Yak Pharm. Co., which is equipped with a Korean good manufacturing practice (KGMP) facility. Participants in the KO and KA groups will be prescribed KRTE three times a day at a dose of 7.4 g after meals for 4 weeks.

**Table 1 T1:** Components of KRTE (7.4 g/dose)

Scientific Name	Amount (g)
*Schizoneptae Herba*	0.27
*Forsythiae Fructus*	0.34
*Ledebouriellae Radix*	0.65
*Angelicae gigantis Radix*	0.70
*Cnidii Rhizoma*	0.65
*Paeoniae Radix*	0.32
*Bupleuri Radix*	0.59
*Aurantii Fructus*	0.86
*Scutellariae Radix*	0.67
*Gardeniae Fructus*	0.89
*Angelicae dahuricae Radix*	0.35
*Platycodi Radix*	0.51
*Glycyrrhizae Radix*	0.67
**Total**	**7.40**

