#### Acupuncture

Certified acupuncture practitioners who have a minimum of 3 years of clinical experience obtained after a 6-year oriental medical college course will perform the acupuncture treatment. They will take a one-day training course for this trial. This course will include the study protocol, methods for acupuncture treatment, and basic information on clinical research. Eight sessions of acupuncture treatment will be performed twice per week for four weeks in patients who will be assigned to the AO and KA groups. Patients will receive acupuncture treatment at 11 classical acupuncture points and/or *ah shi *points that were randomly selected at papules and nodules on the face by the acupuncture practitioner. The following 11 acupuncture points will receive bilateral treatment: ST2 (*Sibai*), ST6 (*Jiache*), ST36 (*Zusanli*), LI20 (*Yingxiang*), LI11 (*Quchi*), PC6 (*Neiguan*), HT8 (*Shaofu*), SP3 (*Taibai*), SP6 (*Sanyinjiao*), SP10 (*Xuehai*), and LR3 (*Taichong*). These points will be treated with 0.25 × 30 mm disposable acupuncture needles (Dongbang Co., Korea). Selection of these acupuncture points was based on a literature review and previous studies of acupuncture treatment of acne vulgaris [20,21] and from the attending doctor's clinical experience and they will be located according to WHO standard Acupuncture Point Locations in the Western Pacific Region [32]. Patients will remain in a supine position for 15 minutes during acupuncture treatment. Papules and nodules will not be artificially extruded.

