#### Waiting list group

Participants who will be assigned to the WL group will not receive any acupuncture or KRTE treatment throughout the 4-week post-randomization period. After the end of the study, if participants elect to undergo acupuncture treatment, it will be provided twice weekly for 4 weeks.

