#### Baseline data and Outcome data

A two-way analysis of covariance (ANCOVA) test will be used to examine the percentage change of inflammatory and non-inflammatory lesions from baseline to the end of the trial when controlling for baseline and other covariates. A repeated measured ANCOVA test will be performed for evaluation of any significant difference in count of inflammatory and non-inflammatory lesions, Skindex-29 score, and VAS score between baseline and the end of the trial. If there is an interaction between KRTE and acupuncture, only the interaction will be shown. If not, the main effect of KRTE and acupuncture will be reanalyzed and presented. According to 'improvement' or 'no-improvement' of IGA score between baseline and the end of the trial, the difference among the groups will be evaluated using a Chi-square test or Fisher's exact test.

Proportion of drop-outs and compliance with KRTE and questionnaire completion will be calculated and described as n (%). The percentage of subjects in each group will be compared using a Chi-square test or Fisher's exact test.

All adverse events reported during the study will be included in the case report forms; the incidence of adverse events will be calculated. The percentage of subjects with adverse events in each group will be calculated and compared using a Chi-square test or Fisher's exact test.

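### With an untreated waiting-list cell and no participant blinding, the KRTE-by-acupuncture interaction concerns treatments as delivered and cannot by itself show antagonism, so it should not be reported alone

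*Protocol article*

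**What the plan says.** The Design section describes a "randomized, 2 × 2 factorial, waiting list controlled, assessor single blinded and single-center pilot trial". No placebo KRTE or sham needling is described under Intervention. Both treatments are open: "Participants in the KO and KA groups will be prescribed KRTE three times a day", and for the AO and KA groups "Eight sessions of acupuncture treatment will be performed twice per week for four weeks". The WL group "will not receive any acupuncture or KRTE treatment throughout the 4-week post-randomization period".

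Under Objective, the first null hypothesis is that "there is no interaction of KRTE and acupuncture treatment on mean percent change of inflammatory acne lesions". The second and third compare KRTE and acupuncture, each against the waiting list, on the same outcome.

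The section Baseline data and Outcome data plans a two-way ANCOVA and then sets a reporting rule: "If there is an interaction between KRTE and acupuncture, only the interaction will be shown". Main effects are presented only when there is no interaction.

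**The concern.** A 2 × 2 interaction asks whether the combination does more or less than the sum of its parts. Here three cells hold people who know they are being treated and one holds people who know they are not. Part of any improvement in KO, AO and KA may come from being treated at all, through expectation, attention or behaviour. If that part does not double when a second treatment is added, the sum KO + AO counts it twice while KA contains it once. The combination then looks less than additive even when the two treatments do not interact.

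Interaction is the first stated hypothesis and a declared reason for the factorial design. A less-than-additive estimate could be read as herbal medicine and acupuncture working against each other, and that reading could enter the planning of the large trial. The same shift could hide a true synergy. The reporting rule makes both errors harder to notice. Once an interaction is declared, the ambiguous contrast stands alone, without the KO − WL and AO − WL comparisons that answer hypotheses 2 and 3, and without the add-on comparisons that bear on combined use, the practice the Background describes.

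**Working it through.** **Inputs from the protocol.** Four cells, 1:1:1:1, 11 per group, 44 in total, assumed drop-out 10% (11 × 0.9 = 9.9, about 10 completers per group). The analysis is a two-way ANCOVA with 95% confidence intervals, which I read as a two-sided 5% test. The Sample size section gives no effect size, SD or power, so the plan has no figure on this point to reproduce.

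**Assumptions, not in the protocol.** Effects are scored as improvement in units of the residual SD. There are no specific effects and no true interaction. The non-specific response is d in KO and in AO, 0 in WL, and (2 − f)·d in KA, where f = 0 means the two responses add fully and f = 1 means they are fully shared.

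**Bias of each contrast.**
- Interaction, KA − KO − AO + WL: (2 − f)d − d − d + 0 = −f·d.
- KO − WL and AO − WL: d each.
- KA − KO and KA − AO: (2 − f)d − d = (1 − f)·d each.
- Each marginal main effect, the mean of its two simple effects: [d + (1 − f)d]/2 = d(1 − f/2), which is d/2 at f = 1.

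**Unequal responses.** If KO and AO carry a and b, and KA shows only the larger, the interaction bias is max(a, b) − a − b = −min(a, b).

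**Chance of a significant interaction.** SE = SD·√(4/n) with n per cell, which at n = 11 is 0.603 SD. The test uses a noncentral t with df = 4(n − 1) − 1, which is 39 at n = 11 and 35 at n = 10. The result depends only on the product f·d:

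| f·d (SD) | for example | n = 11 per cell | n = 10 per cell |
|---|---|---|---|
| 0 | f = 0, any d | 5.0% | 5.0% |
| 0.25 | d = 0.5, f = 0.5 | 6.9% | 6.7% |
| 0.5 | d = 0.5, f = 1 | 12.8% | 12.0% |
| 1.0 | d = 1.0, f = 1 | 36.6% | 33.7% |

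Two further fully shared cases at n = 11: d = 0.3 gives 7.7% and d = 0.8 gives 25.3%.

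**Scale of the pilot.** A true interaction would need to be about 1.7 SD (n = 11) or 1.8 SD (n = 10) for 80% power. Moderate biases will usually move the estimate without reaching significance.

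**If the same design were enlarged.** With an assumed 100 per arm and full sharing, the rates are 32%, 70% and 98% for d = 0.3, 0.5 and 0.8 SD. With d = 0.5 half shared, the rate is 24%. The protocol specifies neither the size nor the design of a later trial, so these figures only show how the bias behaves as the standard error shrinks.

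**The case against.** The strongest reply is that the design is deliberate. The Background lists rare use of a waiting-list control among the gaps in earlier studies, the Design section declares one, and hypothesis 1 is not restricted to specific effects. The interaction of treatments as delivered versus no treatment is a legitimate quantity, and the protocol nowhere says it will conclude antagonism. This stands. A reader might infer that hypothesis 1 cannot be read as an interaction at all; the documents do not support that.

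A reader might also infer that WL participants have no contact and no expectation. That goes too far. Under Secondary outcomes, VAS and IGA are checked at every session with no exception stated for WL, and after the study, "if participants elect to undergo acupuncture treatment, it will be provided twice weekly for 4 weeks". What the text supports is that WL is the only cell without treatment. The skin-care route is narrowed too, since the no-concomitant-therapy rule and the makeup and sunscreen instruction are written for all patients.

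The bias depends on sharing. At f = 0 it vanishes, and nothing in the documents fixes f or d. The primary outcome is a lesion count by a blinded assessor, which limits assessment bias but not participants' own response or behaviour. The self-reported VAS and Skindex-29 are more exposed, but they are outside hypothesis 1.

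Finally, KA − KO and KA − AO might be taken as clean contrasts because both sides are treated. They are clean only at f = 1. At f = 0 they carry the full d while the interaction carries none.

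These points limit the claim but do not remove it. The protocol neither states nor defends additivity of the non-specific responses, and its reporting rule is explicit, so this is not detail left to another document.

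**Conclusion.** The point holds in a limited form. The planned contrast is a valid interaction of KRTE and acupuncture as delivered versus no treatment, but it cannot distinguish specific antagonism from an overlapping non-specific response. The bias is −f·d. At 11 per arm with d = 0.5 SD, the chance of a significant interaction runs from 5% (f = 0) through about 7% (f = 0.5) to about 13% (f = 1), so even under full sharing about 87% of such pilots would show no significant interaction. The documents therefore do not support saying that this trial will, or probably will, report a spurious antagonism. The main risk is a shifted estimate, read without its companion contrasts, passing into the planning of the large trial. All values of d and f are assumptions. The change is worth making because the reporting rule is stated outright and costs little to replace.

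**What to change.** 1. In Baseline data and Outcome data, replace the rule that shows the interaction alone. Always report the interaction estimate with its 95% CI, together with the four simple effects KO − WL, AO − WL, KA − KO and KA − AO with their 95% CIs, all from the planned two-way ANCOVA.
2. There and under Objective, describe the interaction as that of the treatments as delivered, and state that antagonism will not be concluded from a less-than-additive result alone.
3. Describe KO − WL and AO − WL as effects versus no treatment, including non-specific effects.
4. Note that KA − KO and KA − AO are free of the non-specific component only if it is fully shared, and otherwise retain (1 − f)·d.

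All four arms stay. The cost is wording and a few contrasts from a model already planned, with no added patients or visits. The downside is a more modest claim about interaction and efficacy.

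### Null hypotheses 2 and 3 are worded against the waiting list arm, but the planned main effects answer them only if the two treatments act additively

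*Protocol article*

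**What the plan says.** The Objective section of the protocol article gives three null hypotheses on the primary endpoint, percent change in inflammatory lesions. The first is that "there is no interaction of KRTE and acupuncture treatment on mean percent change of inflammatory acne lesions". The second is that mean change "is equal in both the KRTE treatment group and the waiting list group". The third is that it "is equal in both the acupuncture treatment group and the waiting list group".

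The waiting list group is a single arm. Under Randomization and blinding it is one of four groups allocated 1:1:1:1, and the Waiting list group section states: "Participants who will be assigned to the WL group will not receive any acupuncture or KRTE treatment throughout the 4-week post-randomization period".

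Under Baseline data and Outcome data, "A two-way analysis of covariance (ANCOVA) test will be used to examine the percentage change of inflammatory and non-inflammatory lesions". Reporting then depends on the interaction: "If there is an interaction between KRTE and acupuncture, only the interaction will be shown"; otherwise "the main effect of KRTE and acupuncture will be reanalyzed and presented". That section names no contrast of KRTE only, or acupuncture only, with waiting list.

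**The concern.** The hypotheses and the analysis use different comparators. In a 2 × 2 layout the KRTE main effect sets KO+KA against WL+AO, so half of its comparator receives acupuncture. The acupuncture main effect sets AO+KA against WL+KO, so half of its comparator receives KRTE. Hypotheses 2 and 3 name the waiting list arm alone.

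If the main effect is taken as the decision on hypothesis 2, a rejection could come wholly from the combined arm while KRTE alone does no better than waiting. If an interaction is found, the plan as written shows nothing that bears directly on hypotheses 2 and 3, although that is when the effect of each treatment alone is of most interest.

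**Working it through.** **Inputs from the protocol article.** Four arms, 1:1:1:1; 11 per arm, 4 × 11 = 44; drop-out 10%, so 11 × 0.9 = 9.9, about 10 completers per arm. Intention to treat with last observation carried forward could keep up to 11 per arm in the analysis, so both 10 and 11 are shown. The article gives no SD, effect size or power, and no level for the interaction test.

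**Assumptions.** Effects in SD units; normal data with equal variance; two-sided 5% for every test, in line with the stated 95% confidence interval; no covariates. Adjustment would change precision but not the identity in step 1.

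**Step 1: what the main effect estimates.**
- Interaction I = KA − AO − KO + WL.
- KRTE main effect = [(KO − WL) + (KA − AO)]/2.
- Since KA − AO = (KO − WL) + I, the main effect = (KO − WL) + I/2.
- In the same way, the acupuncture main effect = (AO − WL) + I/2.

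The main effect and the contrast with waiting list are the same quantity only when I = 0.

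**Step 2: can the interaction test show that I = 0?** Its standard error is SD × √(4/n). With n = 11 this is 0.603 SD. Power by normal approximation is Φ(I/0.603 − 1.96). For I = 1.0 SD: Φ(1.658 − 1.960) = Φ(−0.302) = 0.38. For 0.8 SD it is 0.26 and for 0.5 SD 0.13. Interactions of this size would usually be missed.

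**Step 3: behaviour of the two-stage rule when hypothesis 2 is true.** Set KO = WL and KA = AO + I. Test the interaction; if it is not significant, test the KRTE main effect. Results from 200,000 simulated trials per row:

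| n per arm | I (SD) | Interaction not significant | Main effect significant, among those | Both, of all trials | Direct KO−WL test significant |
|---|---|---|---|---|---|
| 10 | 0 | 95% | 4.9% | 4.7% | 5% |
| 10 | 0.25 | 93% | 6.5% | 6.1% | 5% |
| 10 | 0.5 | 88% | 11.7% | 10.3% | 5% |
| 10 | 0.8 | 77% | 22.8% | 17.5% | 5% |
| 10 | 1.0 | 66% | 32.8% | 21.7% | 5% |
| 11 | 0 | 95% | 5.0% | 4.8% | 5% |
| 11 | 0.5 | 87% | 12.4% | 10.8% | 5% |
| 11 | 1.0 | 63% | 35.5% | 22.5% | 5% |

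At I = 1.0 SD the main effect has a true value of 0 + 1.0/2 = 0.50 SD, while KO − WL is 0. The size of the acupuncture effect does not matter here, because it cancels from both the KRTE main effect and the interaction.

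**Step 4: precision of the two contrasts.** Half-width of the 95% interval = t × standard error, with 4(n − 1) degrees of freedom.
- n = 10 (t = 2.028): KO − WL, 2.028 × √(2/10) = 0.91 SD; main effect, 2.028 × √(1/10) = 0.64 SD.
- n = 11 (t = 2.021): KO − WL, 2.021 × √(2/11) = 0.86 SD; main effect, 2.021 × √(1/11) = 0.61 SD.

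**The case against.** The strongest reply is that the plan is a sequence. Main effects appear only when no interaction is found, and without interaction the main effect and the contrast with waiting list are the same parameter, estimated more precisely. Pooling is what the factorial design is for. This stands as a limit on the point. A reader might infer that the analysis never tests hypotheses 2 and 3; the protocol does not support that, because under additivity it does. What remains is that a non-significant interaction in 44 patients is weak evidence of additivity.

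A second reply is loose wording. The Objective speaks of treatment groups, not of the arms labelled as receiving one treatment only, so the KRTE side might mean KO+KA. That is possible, and a firm reading of hypothesis 2 as 11 against 11 is an interpretation. But the waiting list side cannot mean WL+AO or WL+KO, so a mismatch remains on either reading.

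Third, a reader might infer that a significant main effect will be reported as superiority over waiting list. The protocol says only that main effects will be presented, and a result labelled as a main effect is not false. The rejection rates above count as errors only if that result is taken as the verdict on hypothesis 2. A reader might also take 22% as the trial's error rate; it is the top of an assumed range.

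Fourth, contrasts after a significant interaction are often left to an analysis plan, which is not at hand. That is fair, so the missing test in that branch carries less weight than the conflict in comparators. Finally, this is a pilot, where strict error control matters less, though the article does state formal efficacy hypotheses.

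**Conclusion.** The point holds in a conditional form. The Objective and the analysis section conflict on the comparator, and the planned main effects answer hypotheses 2 and 3 only if the treatments act additively. The identity needs no assumption about data. The size of the consequence does: with hypothesis 2 true, the two-stage rule rejects it at close to the nominal rate if there is no interaction, at about double that rate for a moderate interaction and at over four times that rate for an interaction of 1 SD. By symmetry the same applies to hypothesis 3. In a pilot, and with a remedy that is mainly wording, this should be corrected but does not invalidate the design.

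**What to change.** Restate hypotheses 2 and 3 as factorial margins: KRTE against no KRTE, averaged over acupuncture, and acupuncture against no acupuncture, averaged over KRTE. Report KO−WL, AO−WL and KA−WL from the same ANCOVA as supportive contrasts with 95% confidence intervals, whatever the interaction result.

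If the comparison with waiting list is the real question, keep the hypotheses, name KO−WL and AO−WL as their tests, and do not use the main effects for the decision.

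Either route needs changes of wording and a few contrasts from a model already planned; no extra patients or data are required. The cost is precision: contrasts with waiting list have intervals about √2 times as wide as the main effects. On the first route, statements about either treatment alone against no treatment become supportive only.
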